### Previous Study by the Research Team

In another recent study, 35 older adults with AD were treated in 3 TPS sessions, with 6,000 pulses in each session for 2–4 weeks, over the dorsolateral prefrontal cortex, areas of the memory and language network, and/or global brain stimulation. Results showed significant improvement in the Consortium to Establish a Registry for Alzheimer's Disease (CERAD) score (immediately after intervention and at 1- and 3-month after intervention). Functional MRI (fMRI) also showed significantly increased connectivity within the memory network (28). Beisteiner's study also found that participants' depressive symptoms were significantly improved as measured by Geriatric Depression Scale (GDS) (*p* = 0.005) and Beck Depression Inventory (BDI) (*p* < 0.0001) at 1- and 3-months post-stimulation follow-up compared with the baseline scores (28). Increased connectivity in memory network was also evident in Beisteiner's study (60) in the 3-months post-stimulation follow-up. Hence, we believed that a 3-month follow-up time span is sufficient to measure the long-term effects of TPS.

The aims of this study are to (1) evaluate the effects of TPS on symptoms of depression among young adults in Hong Kong; (2) improve young adults' anhedonia symptoms after the 2-week TPS intervention and will be maintained at 3-month post-intervention follow-up; (3) improve young adults' instrumental activities of daily living (IADL) after the 2-week TPS intervention and will be maintained at 3-month post-intervention follow-up; (4) improve young adults' cognition after the 2-week TPS intervention and will be maintained at 3-month post-intervention follow-up; (5) evaluate if there are any structural and functional connectivity in participants' brain after the 2-week TPS intervention compared to pre-TPS MRI scan.

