**Secondary objectives**:

To improve young adults' anhedonia symptoms after the 2-week TPS intervention and will be maintained at 3-month post-intervention follow-upTo improve young adults' instrumental activities of daily living (IADL) after the 2-week TPS intervention and will be maintained at 3-month post-intervention follow-up.To improve young adults' cognition after the 2-week TPS intervention and will be maintained at 3-month post-intervention follow-up.Post-MRI scan will show a remarkable structural and functional connectivity in participants' brains after the 2-week TPS intervention compared to pre-MRI scan.

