### Interventions

#### Explanation for the Choice of Comparators

All participants involved will receive TPS treatment. The comparing groups were referred to as the waitlist control group. At the same timepoints, we will appropriately compare the effect of the TPS treatment between those who received it in the intervention group and those who did not receive it in the waitlist control group (62).

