### Statistical Methods

#### Statistical Methods for Primary and Secondary Outcomes

##### Data Analysis Plan

Data will be analysed by the SPSS for Windows, version 27. The normality of the primary outcome (depression) scores will be tested by the Kolmogorov-Smirnov test. If significant differences between sociodemographic variables are found, covariates will be used as a control or confounding variables in the main analysis. For Objective 1, multilevel modelling analysis will be used to investigate changes in the outcome measures (depression) at each time interval (2 weeks and 3 months) with respect to their baseline measurements to examine the effects of TPS. A two-level model will be built, with repeated time points at level 1 and respondents at level 2. The baseline difference between groups will be tested using the Wald test based on the regression coefficient estimates of the indicator. The changes in the outcome measures over time will be included in the fixed part of the model to estimate change from baseline to 2 weeks and from baseline to 3 months. To assess the effects of TPS over time, interaction terms will be included in the fixed part of the model. The significantly different demographics between groups identified in step one of the analysis and other possible confounders will be adjusted by including them in the main-effect model. The within-respondent random effects of the outcome measurements will be taken into account by the level-2 variance in the model. For Objectives 2, 3, and 4, pairwise comparison and other hypotheses on the intervention effects will be tested using a generalised Wald test with an adequate degree of freedom from the modelling analysis (70). The same model, which will be conducted separately for each outcome, will be used to investigate the effect of interventions on secondary outcome measures. To assess the effects of TPS, an intention-to-treat (ITT) analysis will be performed on all participants who undergo random allocation. A multiple imputation method will be used to handle missing data. The pooled results of the multilevel analyses with five multiple imputations will be presented. A sensitivity analysis will be performed by comparing results from analysis datasets with and without missing data imputation. In all tests, significant differences between groups will be detected with a 95% CI, and *p*-values of < 0.05 (two-tailed) will be considered significant. For Objective 5, the neurological rs-fMRI data, longitudinal VBM will be used to examine whether TPS produces local changes in grey matter. Specifically, relative local increases and decreases between pre- and post-intervention scans will be compared within and between study groups. The diffusion MR data will be analysed using the diffusion tensor model. After a mathematical diagonalization process, the eigenvectors and eigenvalues describing the tensor ellipsoid will be determined. Then, two standard diffusion indices will be obtained which are the following: (1) the apparent diffusion coefficient and (2) the fractional anisotropy. DTI scans pre- and post-treatment will permit the assessment of changes in axial diffusivity, with lower values being interpreted as the structural enhancement of white matter. For the cognitive data analysis, general linear modelling (GLM) will be used to compare the difference in performance in the forward and backward digit span, the Stroop test, the category verbal fluency test, and the TMT Parts A and B between the TPS group and the waitlist control group. Performance on the TMT between the TPS group and the waitlist control group will be analysed by one-way repeated-measures ANOVA. Participants' narrative feedback on TPS will be analysed with descriptive content analysis.

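### Objective 5 (imaging) is worded as a pre-to-post comparison, and the DTI and VBM plans do not make the contrast with the waitlist arm decisive, so a within-arm structural change can be credited to TPS

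*Protocol article*

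**What the plan says.** **Comparator for the trial.** Under Explanation for the Choice of Comparators, and in similar terms under Trial Design, the article says it will, at the same timepoints, "compare the effect of the TPS treatment between those who received it in the intervention group and those who did not receive it"; the untreated participants meant here are those on the waitlist.

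**Objective 5.** The list of secondary objectives states: "Post-MRI scan will show a remarkable structural and functional connectivity in participants' brains after the 2-week TPS intervention compared to pre-MRI scan". The fifth aim, at the end of Previous Study by the Research Team, likewise looks for changes "in participants' brain after the 2-week TPS intervention compared to pre-TPS MRI scan". Neither mentions the waitlist arm.

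**Structural analyses (Data Analysis Plan).**
- VBM: "longitudinal VBM will be used to examine whether TPS produces local changes in grey matter". The comparison follows: "relative local increases and decreases between pre- and post-intervention scans will be compared within and between study groups".
- DTI: "DTI scans pre- and post-treatment will permit the assessment of changes in axial diffusivity". The same sentence then says how a fall is to be read: "with lower values being interpreted as the structural enhancement of white matter". No contrast between arms is stated.

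**Functional analysis (Neuroimaging, under Outcomes).** Resting-state networks are compared between groups by dual regression, with a family-wise error corrected threshold of 0.05.

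**General rule (Data Analysis Plan, just before the Objective 5 text).** Tests are described as detecting differences between groups, two-tailed at 0.05.

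**Scan timing (Abstract and Trial Design).** Participants in each group are scanned before and after the six TPS sessions. The waitlist arm also receives TPS, at a different time.

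**The concern.** A pre-to-post change in one arm mixes any effect of TPS with everything else that differs between two scans: scanner drift, head motion or familiarity at a repeat scan, natural recovery of mood, and changes in medication. A concurrent randomised control removes whatever is shared by both arms, but only if the inference is drawn from the difference between arms.

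For structural imaging, the objective names the participant's own earlier scan as comparator. The DTI text attaches a favourable reading to a change without referring to the control. The VBM text sets a causal question and then admits two kinds of comparison without ranking them. A significant change in the TPS arm alone, or significance in one arm and not the other, could be presented as meeting Objective 5. Such a claim would come from a randomised trial without being a randomised result.

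**Working it through.** **1. The passages side by side**

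| Element | Comparator stated | Between-arm contrast decisive? |
|---|---|---|
| Trial Design; Choice of Comparators | Treated versus not-yet-treated, same timepoints | Yes |
| Objective 5 (aims and secondary objectives) | Own pre-TPS scan | No arm named |
| DTI, Data Analysis Plan | Pre versus post | Not stated |
| VBM, Data Analysis Plan | Within and between groups | Included, not ranked |
| rs-fMRI networks, Neuroimaging | Between groups | Yes |

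The mismatch is therefore confined to the wording of the objective and to the two structural analyses.

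**2. Illustration of size**

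The article gives no imaging effect size, SD or power, so there is no stated figure to reproduce.

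Inputs from the article: 30 participants (Sample Size Estimation), allocation 1:1 (Randomisation, Allocation, and Masking), hence 15 per arm; two-sided 5% (Data Analysis Plan).

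Assumptions: no true TPS effect; one summary measure with normally distributed change scores; a non-TPS shift of d SDs of the change score, the same in both arms.

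*Within-arm test (one-sample t on change, n = 15, 14 df).* The critical value is 2.145. The noncentrality is d × √15 = 3.873d. The rejection rate is P(|T| > 2.145) for a noncentral t.

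*Between-arm test of change (15 v 15, 28 df).* A common shift cancels in the difference of means, so the noncentrality is 0 and the rate is 5% for every d.

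*Either test counts as success.* Simulated with 100,000 runs per value of d. This corresponds to reading the VBM sentence as allowing either comparison to support the claim.

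| d (assumed) | Noncentrality, within-arm | Within-arm | Either test | Between-arm |
|---|---|---|---|---|
| 0 | 0 | 5% | 8% | 5% |
| 0.2 | 0.77 | 11% | 14% | 5% |
| 0.3 | 1.16 | 19% | 22% | 5% |
| 0.5 | 1.94 | 44% | 46% | 5% |

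The first row shows that leaving the choice open costs about 3 points even with no shift.

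**3. Price of the between-arm test**

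The true effect on change detectable with 80% power, two-sided 5%:
- One-sample, n = 15: d = 0.78 (noncentrality 0.778 × √15 = 3.01).
- Two-sample, 15 v 15: d = 1.06 (noncentrality 1.06 × √(15/2) = 2.90).

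The between-arm test has about 56% power at 0.8 SD and 75% at 1.0 SD.

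**The case against.** The strongest reply is that the control arm is in the plan. The rs-fMRI networks, which are the functional half of Objective 5, are analysed between groups. The VBM sentence itself includes a between-group comparison. The general testing rule speaks of differences between groups and makes no exception for imaging. The DTI sentence names no test or threshold, so it may describe only how an index is read. The other secondary objectives are also worded as improvement after TPS with no control named, yet they are tested through a model with interaction terms, so loose wording of an objective does not prove an uncontrolled analysis. Ranking of contrasts can also be left to a fuller document.

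Much of this stands. A reader might infer that the randomised control is bypassed for Objective 5 as a whole; the rs-fMRI plan and the between-group part of VBM rule that out. A reader might also suppose that all 30 scan pairs around TPS will be pooled into one pre-post test; no such analysis is planned, and no figure here rests on it.

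The reply does not clear the structural analyses. The text is not merely silent: it states a pre-to-post comparator twice, gives a DTI change a favourable reading without reference to the waitlist, and expressly admits within-group VBM comparisons. The general sentence does not say which result carries the claim. For the other secondary objectives the analysis text supplies a contrast that repairs the loose wording; for DTI it does not.

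The shift sizes are assumed, and a t-test on one measure simplifies a voxel-wise analysis. The rates also apply only if a within-arm result is taken as evidence, which the article permits but does not declare.

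**Conclusion.** The point holds for the wording of Objective 5 and for the DTI and VBM analyses, and not for rs-fMRI. As written, a within-arm structural change can be credited to TPS, contrary to the comparator that the article sets for the trial. Under an assumed non-TPS shift of 0.2 to 0.5 SD, one measure and 15 participants, the false-positive rate of a within-arm claim is 11% to 44%, against 5% for the between-arm test. With a smaller shift the excess is smaller, and with none a single within-arm test keeps its 5%. The primary depression outcome is untouched. This is a correction that should be made to one secondary objective.

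**What to change.** - Restate Objective 5, in both the aims and the secondary objectives, as the difference between the TPS and waitlist arms in change from first to second scan.
- In the Data Analysis Plan, name the arm-by-time contrast (equivalently, the between-arm test of the post-minus-pre difference) as the deciding test for the DTI indices and VBM, in line with the between-group analysis already set for rs-fMRI.
- Label within-arm changes as descriptive and not as evidence of a TPS effect, and tie the reading of lower axial diffusivity to the between-arm result.
- Reconcile the scan timing in the Abstract and Trial Design with Choice of Comparators, so that the waitlist scan pair used in the contrast has no TPS between its scans. If the waitlist scans instead bracket that arm's own TPS, the between-arm contrast compares treated with treated and the other changes do not help.

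The cost is a few sentences and lower sensitivity: 80% power at about 1.06 SD with 15 per arm, against about 0.78 SD for an uncontrolled pre-post test in 15. If the current schedule provides no untreated waitlist scan pair, obtaining one is a further cost that the article does not allow to be sized.

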#### Neuroimaging

Participants will receive pre- and post-treatment MRI scans to measure any changes in structural and functional connectivity changes in the brain. Structural MRI, diffusion tensor imaging (DTI), and resting state-fMRI (rs-fMRI) will be performed using a 3T scanner at the University Research Facility in Behavioural and Systems Neuroscience, The Hong Kong Polytechnic University. The subjects will be closely monitored by the research assistant and the radiographer during scanning. The whole scan will last around 45 min including preparation. Structural MRI scans, including T1- and T2-weighted fluid attenuation inversion recovery (T2-FLAIR) sequences, will be used for assessing regional volume differences across the whole brain. High resolution sagittal 3D T1-weighted [spoiled gradient recalled echo (SPGR)/magnetisation-prepared rapid gradient echo (MPRAGE)] images of 1 mm x 1 mm x 1 mm were acquired with repetition time (TR) = 1,820 ms, echo time (TE) = 3.75 ms, inversion time (TI) = 1,100 ms, and flip angle = 70°. This will be followed with axial 2D-T2-weighted FLAIR images of 0.9 × 0.9 × 3 mm, which will be acquired with TR = 9,160 ms, TE = 90 ms, TI = 2,500 ms, and flip angle = 150°, for the quantification of white matter hyperintensities (WMH). DTI sequence will be conducted using a single-shot spin-echo echo-planar imaging, with diffusion-sensitising gradients applied along 16 non-collinear directions with diffusion weighting factor b = 1,000 s/mm^2^ and two b = 0 images. The imaging parameters were the following: TR/TE = 1,200/82 ms, matrix size = 128 × 128, field of view (FOV) = 240 mm, slice thickness = 3 mm with no intersection gap, number of excitations = 2, and number of slices = 67. Finally, resting-state fMRI of 150 T2-weighted gradient echo-planar imaging (EPI) will be acquired with TR = 2 s and TE = 32 ms, with 32 slices, and a resolution of 3 × 3 × 4 mm, during which subjects will view a fixation cross (“+”) passively at the centre of the screen. Images processing and analysis will be performed using software packages including FSL (http://fsl.fmrib.ox.ac.uk/fsl/fslwiki/), Freesurfer, and SPM8 (Oxford, UK). Total brain and its total grey and white matter volumes will be extracted from the T1 structural scan. Grey matter and white matter tissue maps will be segmented and compared for regional tissue density differences using voxel-based morphometry (VBM) (69). Structural connectivity will be assessed by fractional anisotropy (FA) maps extracted from DTI imaging.

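### A fall in axial diffusivity is labelled in advance as white-matter enhancement, although it can accompany a decline in fractional anisotropy, the plan's own structural-connectivity measure

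*Protocol article*

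**What the plan says.** Four statements in the protocol article bear on this point.

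- **Secondary objectives.** The imaging objective is worded as an expected result: "Post-MRI scan will show a remarkable structural and functional connectivity in participants' brains after the 2-week TPS intervention compared to pre-MRI scan". It names no index and no sign.
- **Neuroimaging.** The measure is named: "Structural connectivity will be assessed by fractional anisotropy (FA) maps extracted from DTI imaging". No direction of benefit is given for FA.
- **Data Analysis Plan, indices.** After the tensor model is fitted, "the eigenvectors and eigenvalues describing the tensor ellipsoid will be determined", and then "two standard diffusion indices will be obtained which are the following: (1) the apparent diffusion coefficient and (2) the fractional anisotropy".
- **Data Analysis Plan, interpretation.** The sentence that follows turns to a quantity outside that list. It says the scans before and after treatment will allow assessment of "changes in axial diffusivity, with lower values being interpreted as the structural enhancement of white matter".

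The same section sets two-tailed testing at 0.05 for all tests. It gives no reason or source for the reading of axial diffusivity.

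**The concern.** The only direction fixed in advance for any diffusion index belongs to axial diffusivity, which is neither the named structural-connectivity measure nor a listed index. Axial diffusivity and FA are not independent readings: the first is the largest eigenvalue of the tensor and the second is a function of all three. A rule that attaches a favourable label to a fall in one of them needs to be checked against what that fall does to the other.

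What is at stake is interpretation. If the label is applied as written, a report on Objective 5 could describe white matter as structurally enhanced in scans where the measure chosen for structural connectivity went down. The label is set before the data are seen, so a reader would take it as a planned criterion.

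**Working it through.** **Inputs.** The tensor model, the eigenvalues, FA and the axial-diffusivity label come from the Neuroimaging and Data Analysis Plan sections. The protocol gives no eigenvalues, so all those below are assumptions, in units of 10^-3 mm^2/s. There is no figure in the plan to reproduce.

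**Formula.** FA = sqrt(3/2) × sqrt(Σ(λi − mean)²) / sqrt(Σλi²). With axial diffusivity AD = λ1 and radial diffusivity RD = λ2 = λ3, this becomes

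FA = (AD − RD) / sqrt(AD² + 2·RD²).

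**Step 1: what decides the sign.** Put k = RD/AD. Then FA = (1 − k)/sqrt(1 + 2k²), and its derivative in k is −(1 + 2k)/(1 + 2k²)^(3/2), which is always negative. So FA falls exactly when RD/AD rises. When AD falls, that happens if RD is unchanged, rises, or falls by a smaller percentage than AD. If RD falls by the same percentage, FA does not move. If it falls by a larger percentage, FA rises.

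Without the assumption λ2 = λ3, a check on 200,000 random ordered tensors found no case in which FA fell as λ1 rose with the other two eigenvalues held fixed.

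**Step 2: AD falls from 1.4 to 1.2, RD fixed.**

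| RD | FA before | FA after |
|---|---|---|
| 0.3 | 1.1/sqrt(2.14) = 0.752 | 0.9/sqrt(1.62) = 0.707 |
| 0.5 | 0.9/sqrt(2.46) = 0.574 | 0.7/sqrt(1.94) = 0.503 |
| 0.7 | 0.7/sqrt(2.94) = 0.408 | 0.5/sqrt(2.42) = 0.321 |

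In the middle row the relative fall is (0.574 − 0.503)/0.574 = 12%. These rows vary the starting level of RD but not its change, so they do not test what happens when RD moves.

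**Step 3: the same fall in AD, with RD also falling.** AD falls by 0.2/1.4 = 14.3%. If RD goes from 0.5 to 0.4, a fall of 20%, FA becomes 0.8/sqrt(1.76) = 0.603, which is a rise from 0.574.

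**Step 4: AD falls by 10% from four assumed baselines.**

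| AD, RD | Baseline FA | RD +10% | RD fixed | RD −10% | RD −20% |
|---|---|---|---|---|---|
| 1.0, 0.8 | 0.1325 | 0.0130 | 0.0692 | 0.1325 | 0.2037 |
| 1.2, 0.6 | 0.4082 | 0.2942 | 0.3495 | 0.4082 | 0.4704 |
| 1.5, 0.5 | 0.6030 | 0.5135 | 0.5578 | 0.6030 | 0.6490 |
| 1.7, 0.3 | 0.7990 | 0.7502 | 0.7747 | 0.7990 | 0.8231 |

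In every cell AD has fallen, so the plan's label reads enhancement throughout. FA is lower, equal or higher depending on RD, which the label does not consider.

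**The case against.** Much of the case on the other side stands.

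- **The relation is conditional.** A reader might infer that lower axial diffusivity always reduces FA. It does not, as Steps 3 and 4 show.
- **There are not two opposing rules.** A reader might infer that the plan contradicts itself on direction. It fixes a direction for axial diffusivity only. That higher FA means better connectivity is a common reading, but the protocol does not state it.
- **Objective 5 is not shown to be winnable either way.** A reader might infer that it can be declared met whichever way the data go. The protocol links no success criterion for the objective to either index, a rise in axial diffusivity carries no favourable label, and testing is two-tailed.
- **Precedence between indices is ordinary analysis-plan detail.** This is a condensed article and the statistical analysis plan is not shown, so silence on radial diffusivity or on disagreement between indices is not a fault here.
- **The biology is not on trial.** Whether lower axial diffusivity can mark improved white matter cannot be settled from this document.

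What these points do not remove is the clause itself, which is a stated interpretation and not an omission. Two-tailed testing governs the p-value, not the label placed on the result. Nor does the protocol call imaging exploratory: it lists imaging as a secondary objective with an expected result.

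**Conclusion.** The concern holds in a conditional form. The plan labels a fall in axial diffusivity as enhancement, and that label can apply while FA, its own structural-connectivity measure, declines. This happens whenever radial diffusivity is unchanged, rises, or falls proportionally less than axial diffusivity. The sign follows from the definition of FA for a tensor with equal radial eigenvalues; the sizes rest on assumed eigenvalues and are illustrative.

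The finding is that the label is insecure, not that FA and axial diffusivity must conflict or that a decline in FA is defined as harm. Severity is minor. It bears on how one secondary imaging objective would be described, and not on HAM-D-17, the sample size or the main model.

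**What to change.** In the Data Analysis Plan, delete the clause that interprets lower axial diffusivity. Keep FA, as named under Neuroimaging, as the structural-connectivity measure for Objective 5. Compare its pre-to-post change between the TPS and waitlist groups, two-sided and with no presumed direction. The between-group comparison of change is a proposed addition, since the Neuroimaging sentence on FA does not specify one.

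Report axial diffusivity together with radial diffusivity and the apparent diffusion coefficient descriptively, without calling any pattern enhancement. Add axial and radial diffusivity to the list of indices to be obtained, so that the list matches what is reported.

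The cost is wording only. The fitted tensor already supplies every index, so no further scans, participants or visits are needed.

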#### Cognition

Global cognition will be measured using the Hong Kong Chinese version of the Montreal Cognitive Assessment (MoCA) (68). The MoCA is a one-page test with a maximum score of 30. One point is added if the person has 12 years of education or less. A score of 23–26 represents mild cognitive impairment, 17–22 represents moderate impairment, and 16 or below suggests severe impairment and dementia. Working memory, executive function, and attention will be measured by forward and backward digit span, the category verbal fluency test, and the Trail Making Test (TMT) Parts A and B.

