### Data Collection and Management

#### Plans for Assessment and Collection of Outcomes

Both groups will be measured at baseline (T_1_), immediately after the intervention (T_2_), and at the 3-month follow-up (T_3_; refer to Figure 5 CONSORT flow diagram). Based on the previous studies, a 3-month follow-up is sufficient to assess the long-term sustainability of the TPS intervention (60). A trained clinician investigator who is not involved in the intervention will perform the assessments. The primary and secondary outcomes will be assessed at baseline, immediately after the intervention, and 12 weeks after the intervention.

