### Limitations of This Study

There are some limitations that need to be addressed in this protocol. First, since we will execute the first pilot RCT nationwide interrogating the effects of TPS on MDD, we can only use existing NIBS studies like TMS and tDCS to act as a comparison for our findings. Since both TMS and tDCS use non-invasive neuromodulation technology by electrical stimulation, the mechanism will be somehow different from TPS which uses ultrashort ultrasound waves in the stimulation of the human brain. Thus, our findings will need to be interpreted with caution. Second, participants in the waitlist control group will be given the identical TPS intervention, albeit in different timepoints, but they will all receive the same TPS pulse/frequency/energy in this TPS trial. Third, the TPS machine itself may have a potential placebo effect which may bias the results. Fourth, there could be a potential risk of contamination if our waitlist control group utilised self-prescribed pharmaceutical input or other TCM modalities (e.g., herbal soup and acupuncture) to treat their symptoms of depression while waiting the TPS treatment. Such contamination may impact the receptivity and efficacy of our TPS intervention. Fifth, participants will be administered the same sets of psychological instruments at three different time points so there is a potential risk that some participants may recall some contents of these instruments. To prevent this, our research personnel will not provide accurate answers to these tests throughout each study phase to minimise recall bias. Last but not least, individuals with severe depression with fleeting suicidal ideas will be excluded in this study, and thus, the efficacy of TPS on these severely depressive and suicidal community-dwelling individuals will remain unknown. Future replication of a multi-centre study may adopt a double-blinded, sham-controlled RCT to philtre out the placebo effects on a larger sample.

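### The Trail Making Test is to be compared between arms by a one-way repeated-measures ANOVA, which has no arm term; two other analyses also cover it with no rule on which governs, and a Stroop test is analysed but not listed as an outcome measure

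*Protocol article*

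**What the plan says.** All the analysis statements stand in one section of the protocol article, the Data Analysis Plan.

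- Secondary outcomes in general take the two-level model set out for depression, with time points nested in respondents and interaction terms for the effect of TPS over time: "The same model, which will be conducted separately for each outcome, will be used to investigate the effect of interventions on secondary outcome measures". Cognition is a secondary outcome, so the TMT falls under this model.
- A later sentence on the cognitive data applies a general linear model to between-arm differences in "the forward and backward digit span, the Stroop test, the category verbal fluency test, and the TMT Parts A and B".
- The sentence directly after it reads: "Performance on the TMT between the TPS group and the waitlist control group will be analysed by one-way repeated-measures ANOVA".

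The Cognition section names the Montreal Cognitive Assessment for global cognition. Of the more specific cognitive domains it says that they "will be measured by forward and backward digit span, the category verbal fluency test, and the Trail Making Test (TMT) Parts A and B". The Stroop test is not in that list and appears nowhere else in the article.

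On timing, Plans for Assessment and Collection of Outcomes says: "The primary and secondary outcomes will be assessed at baseline, immediately after the intervention, and 12 weeks after the intervention". The Limitations section accepts that "participants will be administered the same sets of psychological instruments at three different time points" and that participants may recall some of the content.

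**The concern.** The named test does not match its stated purpose. Taken literally, a one-way repeated-measures ANOVA asks whether mean TMT performance changes across the three assessments. It does not ask whether it changes differently in the two arms. Repeating a timed cognitive test can itself produce change over time, and any such gain shared by both arms would fall on the only factor in this ANOVA.

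The TMT also has three stated analyses and no order among them. They can give different answers, and the plan would allow the choice to be made after the results are seen. Separately, the analysis list and the outcome list disagree about the Stroop test, so one of them is wrong.

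What is at stake is the cognition objective, one of the secondary objectives. The HAM-D-17 analysis is untouched.

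**Working it through.** **Step 1: what each stated analysis can test.**

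| Analysis in the Data Analysis Plan | Arm term | Arm-by-time term |
|---|---|---|
| Two-level model, one per secondary outcome | yes | yes (interaction terms stated) |
| General linear model on the cognitive tests | yes | not stated |
| One-way repeated-measures ANOVA on the TMT | no | no |

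The third is the most specific statement about the TMT, and it is the only one that cannot compare arms.

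**Step 2: the two lists of cognitive tests.** Cognition section: Montreal Cognitive Assessment, digit span forward and backward, category verbal fluency, TMT A and B. Linear-model sentence: digit span forward and backward, Stroop, category verbal fluency, TMT A and B. The Stroop test is the unmatched addition.

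**Step 3: size of the possible error if the ANOVA is run as named.** The article gives no figure to reproduce: no TMT effect, SD, retest correlation or power calculation.

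*Inputs from the article:* 30 participants; 1:1 allocation, so 15 per arm; three assessments; two-sided 0.05.

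*Assumptions, not from the article:* no TPS effect; the same retest gain d, in SD units, in both arms at the second and third assessments; d = 0.2, 0.3 or 0.5; within-person correlation r = 0.5, 0.7 or 0.8, equal between all pairs of assessments; normal data.

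*Formula.* The time means are 0, d, d, with mean 2d/3. Their squared deviations sum to (4/9 + 1/9 + 1/9)d² = (2/3)d². The time F-test has 2 and 2(n − 1) degrees of freedom and noncentrality λ = n × (2/3)d² / (1 − r). For n = 30 this is 20d²/(1 − r), with 2 and 58 degrees of freedom.

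- Smallest case, d = 0.2, r = 0.5: λ = 20 × 0.04 / 0.5 = 1.6, and the time test is significant in 18% of trials.
- Middle case, d = 0.3, r = 0.7: λ = 20 × 0.09 / 0.3 = 6.0, giving 56%.
- Largest case, d = 0.5, r = 0.8: λ = 20 × 0.25 / 0.2 = 25, giving 99.5%.

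A simulation of 20,000 trials per setting agrees with these values. Its results for the time test with all 30 participants pooled are:

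| Shared gain | r = 0.5 | r = 0.7 | r = 0.8 |
|---|---|---|---|
| 0 | 5.0% | 5.2% | 4.8% |
| 0.2 SD | 18.1% | 27.8% | 39.8% |
| 0.3 SD | 36.3% | 55.7% | 74.6% |
| 0.5 SD | 79.7% | 95.5% | 99.5% |

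Run within one arm of 15, the rates over the same correlations are 11% to 20% for a gain of 0.2 SD, 19% to 41% for 0.3 SD, and 45% to 86% for 0.5 SD.

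**Step 4: the same trials with an arm-by-time test.** The interaction F-test of a two-factor mixed ANOVA (2 and 56 degrees of freedom) is significant in 4.8% to 5.2% of trials in every setting. A gain shared by both arms cancels out of that contrast.

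**The case against.** The strongest reply is that a group-by-time ANOVA was meant and misnamed. The sentence speaks of a comparison between the two arms, the same section looks for between-group differences in all tests, the Trial Design section describes two-armed repeated measures, and the Abstract names a repeated-measures ANOVA without calling it one-way. This is a plausible reading. If it is right, the false-positive figures above do not apply, but the test is still misnamed and the text still needs correcting.

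A second reply is that valid arm comparisons of the TMT are already planned, through the two-level model and the linear model. That is true and limits the damage. Since a repeated-measures ANOVA is itself a linear model, the last sentence might also be read as detail on the one before it, leaving two analyses rather than three. On either count, nothing says which result answers the cognition objective.

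A third reply is that the percentages rest on assumed gains and correlations. They do, which is why a range is given.

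Two stronger readings are tempting and not supported. A reader might infer that the plan will report practice gains as a TPS effect. The article nowhere says that a time main effect would be read that way, so this remains conditional. A reader might also infer that the Stroop test is never administered. The article shows only that it is missing from the listed measures.

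**Conclusion.** The point holds on the text. The test named for the TMT cannot make the between-arm comparison assigned to it, the TMT has overlapping analyses with no governing one, and the Stroop test is analysed without being listed as an outcome measure.

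The inflation of roughly 18% to 99.5%, against a nominal 5%, is conditional. It requires that the ANOVA is run literally on all 30 participants, that its time effect is taken as a TPS effect, and that shared retest gains and correlations lie in the assumed ranges. The wording defect does not depend on any of these.

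The matter is confined to cognitive measures under one secondary objective. It should be corrected before those data are analysed, but it does not bear on the primary result.

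**What to change.** 1. Delete the one-way repeated-measures ANOVA sentence.
2. Name the two-level model with arm-by-time interaction terms, already stated in the Data Analysis Plan, as the single governing analysis for TMT A and B and the other cognitive tests. Report the between-arm difference in change from baseline at both 2 weeks and 3 months, because the cognition objective covers maintenance as well as the immediate effect. Replacing this with a baseline-adjusted contrast at 2 weeks alone would be a different model and would drop the maintenance part.
3. Drop the separate general linear model, or label it supportive.
4. Remove the Stroop test from the Data Analysis Plan. If it is in fact administered, add it to the Cognition section instead.

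Items 1 to 3, and removal of the Stroop test, are changes of wording only; no participants, visits or data are added. Listing the Stroop test as a measure would change the outcome measurements, which the section on communicating protocol amendments says must be notified to the IRB and the university's research ethics committee. The Trial Status section reports recruitment as complete, which is no obstacle to any of these changes.
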